| HIV ELISA                     |           |                                      |           |                       |                            |          |          |          |          |          |          |          | x e |

a Number of monthly pre-natal visits will vary from 1-3 depending on how early mother is enrolled in third trimester; when possible the baseline visit (BL) will typically be the same as the -3 visit.

b A physical examination will be conducted and nutritional assessment performed including weight, height, 3-site skinfold thickness (triceps, subscapular and suprailiac) and upper arm, and waist and hip circumference. During pregnancy measurements will include only, height, weight, mid arm circumference and triceps skinfold thickness. Fat free body mass and percent body fat will be calculated from anthropometric measurements using the equations of Durnin et al. Upper arm circumference and triceps skinfold measures will be used to calculate mid-arm muscle circumference or area.

c Pro-inflammatory cytokines IL-6 and IL-8 and sIgA will be measured as described below

dPercentage fat content will be measured by standard creatatocrit.

ePlasma will be frozen and stored for possible additional assays of nutritional, virologic and/or immunologic status.

Scientific Protocol, version 1.1

July 6, 2017

**7. Sample size.** The primary endpoint will be infant weight at 3 months. Our hypothesis is that infants of mothers in the active PCS treatment group will have a median 3 month weight 0.5 kg higher than infants of mothers in the MNS control group. The standard deviation of infant weight at 2 months among HIV infected infants born on the African continent is approximately 0.7 kg (IQR of 4.0 to 4.9kg; Violari NEJM 2008). We plan to enroll 96 women in the third trimester of pregnancy, and randomize 48 to each arm. We anticipate that at least 95% of enrolled mothers will give birth to a live infant who survives to 3 months, and that no more than 5% of these mother-infant pairs will be lost to follow-up. Thus we anticipate obtaining the primary endpoint on 85 infants. This gives us 80% power to detect effects of nutrition on infant weight at 3 months of 0.50 kilograms. (1.1 pounds).

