**8. Data analysis.** For the primary endpoint, median infant weight, will be compared between the two groups at 3 months using intention to treat (ITT) methodology. Multivariate analysis will be used to control for variables which differ between PCS and MNS treatment arms at baseline (e.g. maternal CD4 at baseline, infant birth weight). The secondary endpoint will be maternal BMI at the end of the intervention (6 months after infant birth).

The method of generalized estimating equations will be used to accommodate repeated measurements of infant weight during follow-up. The cluster unit is the subject and the correlation structure will be unstructured. In addition weight at other time points (e.g., birth, 6 months) will be compared between the two arms using a t-test.

We will use two methods to assess the influence of on compliance on endpoints. The first will be an as-treated analysis done using proportion of supplements reported taken as the exposure. We will test if this correlates with infant weight at 3 months using linear regression to adjust for any baseline covariates that are associated with proportion compliance. As-treated analyses are observational analyses that are subject to bias. Thus, the second approach will be to conduct an instrumental variable analysis which has the benefit of avoiding selection bias. Instrumental variable analysis (based on randomization) will yield an unbiased estimate of the effect of compliance on infant weight at 3 months. Subgroup analyses will be conducted on women entering the study in the lowest BMI quartile.

Additional exploratory endpoints will be infant development, infant diarrheal disease, maternal CD4, maternal albumin, breast milk composition, and breast milk immunological parameters.

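### Covariates for the adjusted analysis of 3-month weight are picked by observed baseline imbalance, and a post-randomisation variable (birth weight) is offered as an example

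*Protocol*

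**What the plan says.** Protocol Section 7 sets the endpoint: "The primary endpoint will be infant weight at 3 months". The hypothesis there is a "median 3 month weight 0.5 kg higher than infants of mothers in the MNS control group".

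Section 8 first gives the main comparison: "median infant weight, will be compared between the two groups at 3 months using intention to treat (ITT) methodology". The next sentence adds adjustment: "Multivariate analysis will be used to control for variables which differ between PCS and MNS treatment arms at baseline", with the examples "e.g. maternal CD4 at baseline, infant birth weight".

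The section does not define what counts as differing, closes no list, and does not say how the adjusted result ranks against the comparison of medians. Later in Section 8, weight at birth is itself to be compared between the arms with a t-test.

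Section 1 and Table 2 place the start of the intervention in the third trimester, so birth weight is observed after randomisation and after supplementation has begun. CD4 is scheduled at baseline (Section 3, Table 2). Maternal height, weight and arm circumference are also baseline measurements (Section 3; Table 2, footnote b).

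**The concern.** After randomisation, a difference between arms in a true baseline variable is chance. Its size says nothing about how strongly the variable predicts infant weight. A rule that selects on imbalance therefore tends to leave out strong predictors that look balanced and to bring in weak ones that do not. It also makes the covariate set unknown until the data are in hand, and with no definition of a difference, the analyst has to supply one.

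The birth weight example adds a separate problem. If the supplement works before delivery, the arms will differ in birth weight because of treatment. The rule would then call for adjustment, and the adjusted estimate would leave out the part of the effect that passes through birth weight.

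At stake are precision in a trial of 96 women, the clarity of the primary result, and possibly the meaning of the adjusted estimate.

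**Working it through.** **Inputs from Protocol Section 7.** Effect 0.5 kg; SD "is approximately 0.7 kg (IQR of 4.0 to 4.9kg"); 96 women, 48 per arm; 85 infants with the endpoint; stated power 80%. Alpha is not stated, so two-sided 0.05 is assumed. No correlation between any covariate and infant weight is given, so R2 is an assumption throughout.

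**1. The plan's own figure.** SE = SD × √(4/n) = 0.7 × √(4/85) = 0.152 kg. Power for 0.5 kg is 90.9% by the normal approximation and 90.2% by the noncentral t. The stated 80% is not reproduced; it would need an SD of about 0.82 kg (80.3% normal, 79.3% t). That gap is a separate matter. Both SDs are carried below.

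**2. Gain from fixed prognostic covariates.** The residual SD becomes SD × √(1 − R2), which is equivalent to a trial of 85/(1 − R2) infants. Power is by noncentral t at 0.5 kg.

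| Assumed R2 | SE reduction | Equivalent n | Power, SD 0.7 | Power, SD 0.82 |
|---|---|---|---|---|
| 0 | 0% | 85 | 90% | 79% |
| 0.1 | 5% | 94 | 93% | 83% |
| 0.2 | 11% | 106 | 95% | 87% |
| 0.3 | 16% | 121 | 97% | 91% |

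These are powers for a difference in means. Section 8 speaks of medians without naming a test.

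**3. What the imbalance rule recovers.** A simulation used 43 infants per arm and ten candidate covariates, one of them prognostic, and read a difference as p < 0.05 (assumed, since the protocol gives no threshold). The prognostic covariate entered in about 5% of trials. At least one of the ten entered in about 40%, in line with 1 − 0.95^10 = 0.40. For R2 = 0.25 and a 0.5 kg effect:

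| Analysis | SE, SD 0.7 | Power, SD 0.7 | Power, SD about 0.82 |
|---|---|---|---|
| Unadjusted | 0.152 | 90% | 80% |
| Imbalance rule | 0.149 | 90% | 79% |
| Fixed covariate | 0.130 | 96% | 90% |

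The rule performs almost like no adjustment.

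**4. Type I error.** With no treatment effect, the rule rejected in 0.048 / 0.042 / 0.040 / 0.037 of simulated trials for R2 = 0.10 / 0.25 / 0.36 / 0.50. It is slightly conservative.

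**5. Birth weight as a covariate.** Let the supplement raise birth weight by m kg and let 3-month weight rise by b kg per kg of birth weight (both assumed). Adjustment leaves 0.50 − m × b.
- m = 0.1, b = 0.8: 0.50 − 0.08 = 0.42 kg.
- m = 0.2, b = 1.0: 0.50 − 0.20 = 0.30 kg.

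If the supplement does not change birth weight, m = 0 and nothing is removed in this way.

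**The case against.** **The primary analysis may already be unadjusted.** A reader might infer that the primary result is itself data-driven. The text does not go that far. The intention-to-treat comparison of medians comes first, and the multivariate analysis is never called primary. The natural reading is an unadjusted comparison with supportive adjustment. What stands is that the ranking is not stated.

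**Covariate lists belong in the SAP.** True of a list that is merely absent. For that reason the lack of infant sex or gestational age in Section 8 is not an error: the covariates named are only examples. Nor does the protocol name either as a recorded variable; Table 2 lists an infant ultrasound at baseline without giving its purpose. But Section 8 does not defer the choice. It fixes a selection rule, and an SAP written to comply would inherit it.

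**False positives.** A reader might suspect inflated type I error. The simulation shows none when the rule is followed mechanically. Inflation would need free choice between adjusted and unadjusted results, which the protocol does not propose, although it does not rule it out by ranking them.

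**Uneven prenatal exposure.** Table 2, footnote a, says "Number of monthly pre-natal visits will vary from 1-3 depending on how early mother is enrolled in third trimester". This is not a flaw in itself, because randomisation balances enrolment timing in expectation.

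**Chance imbalance as bias.** An imbalance in a predictor that goes unflagged, such as infant sex, shifts the unadjusted estimate in a single trial. That is ordinary sampling variation already carried by its confidence interval.

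**The benefit is modest.** This stands in part. At the planned effect and SD the gain is 3 to 7 percentage points from an adequate base, and if the covariates predict little, a few degrees of freedom are spent for almost nothing.

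**Conclusion.** The point holds as a correctable weakness in a written rule. Selection on observed imbalance recovers little of the available precision, leaves the adjusted model to be chosen after the data are seen, and sits beside a comparison of medians without a stated ranking. Calling birth weight a baseline variable is a misstatement on the protocol's own timeline, and adjusting for it could understate the effect.

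The size is uncertain. For assumed R2 of 0.1 to 0.3, power at 0.5 kg goes from 90% to 93–97% if the SD is 0.7 kg, and from 79% to 83–91% if it is about 0.82 kg. The second case deserves attention because the 0.7 kg comes from weights at 2 months in HIV-infected infants, so the SD at 3 months in this trial is not known. The loss from adjusting for birth weight depends on an effect on birth weight that the documents do not quantify.

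**What to change.** In Section 8, replace the imbalance rule with a short closed list of covariates measured before randomisation, used whatever the observed balance. Candidates already collected are maternal height, mid-arm circumference or weight, and baseline CD4. Add infant sex and gestational age at enrolment only if the trial records them. Exclude birth weight from this model and keep it as an outcome, as Section 8 already treats it.

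State whether the adjusted or the unadjusted analysis is primary, with the other supportive, and whether the effect is a difference in means or in medians. An ordinary regression estimates a mean difference, so moving to it from the comparison of medians should be an explicit decision.

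The cost is a few sentences and a few degrees of freedom out of about 85. No new measurement is needed for the maternal variables.

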## **DarDar 2-B Nutrition Study Scientific Protocol**

**1. Summary.** The DarDar 2-B Nutrition Study is a randomized, controlled trial of 9 months of a porridge protein-calorie supplement (PCS) and micronutrient supplement (MNS) vs MNS control alone administered to 96 HIV-infected women from Dar es Salaam, Tanzania in their third trimester who plan to exclusively breastfeed for 6 months. The objective is to determine if a PCS will improve health outcomes in these mothers and their infants. The study design is based on an earlier data-gathering study (DarDar 2-A Nutrition Study) which determined dietary intakes, food preferences and the extent of malnutrition in the target group.

Two central issues underscore the rationale for this study: 1) HIV-infected women have increased nutritional demands and/or deficits which are augmented/exacerbated by pregnancy and lactation, and 2) It is highly beneficial for infants in resource-limited settings to breastfeed, even (and especially) in the setting of maternal HIV infection. We hypothesize that optimized nutrition through provision of a culturally acceptable PCS will result in improved maternal and infant health mediated by improved infant growth, improved lactation, better control of maternal viral replication and maintenance of immune function, reduced infant exposure to maternal virus via breast milk, and enhanced maternal-infant transfer of passively acquired immune factors.

**2. Recruitment and eligibility.** HIV-infected women in their second trimester will be recruited by the DarDar Study Nurse from pre-natal clinics at designated hospitals and dispensaries in Dar es Salaam including, but not limited to, facilities at Mbagala, Temeke, Mwananyamala, and Amana Hospitals to begin the study in their third trimester. The protocol will be explained and signed consent obtained. Eligibility criteria include expected residence in Dar during the duration of breastfeeding, willingness to identify a confidante (friend, spouse or relative), minimum age 18 and plan to exclusively breastfeed. Subjects with defined high risk pregnancy (e.g., diabetes, pre-eclampsia) who are typically seen at speciality clinics at district hospitals will be excluded. Subjects with allergy to components of the PCS will also be excluded.

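### Section 8 names infant birth weight as a baseline covariate for the adjusted analysis of 3-month weight, although birth follows randomisation and one to three monthly prenatal visits

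*Protocol*

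**What the plan says.** Protocol Section 7 makes infant weight at 3 months the primary endpoint and hypothesises a 0.5 kg advantage for the porridge supplement (PCS) arm. Section 8 first compares the arms on this endpoint by intention to treat. The next sentence adds a multivariate analysis to "control for variables which differ between PCS and MNS treatment arms at baseline (e.g. maternal CD4 at baseline, infant birth weight").

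Four other places fix the timing and the role of birth weight:

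- Section 2: women are recruited "to begin the study in their third trimester".
- Table 2, footnote a: "Number of monthly pre-natal visits will vary from 1-3 depending on how early mother is enrolled in third trimester".
- Sections 1 and 8: the trial is a "randomized, controlled trial of 9 months of a porridge protein-calorie supplement (PCS"), and the secondary endpoint is "maternal BMI at the end of the intervention (6 months after infant birth"). Nine months ending six months after birth leaves up to about three months before birth.
- Section 8, next paragraph: "weight at other time points (e.g., birth, 6 months) will be compared between the two arms using a t-test".

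Section 1 also expects "improved maternal and infant health mediated by improved infant growth".

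**The concern.** A baseline covariate must be fixed before assignment. Birth weight is measured after assignment and after up to about three months of supplement, so the intervention can change it. It may lie on the path from PCS to 3-month weight. Section 8 thus gives one variable two incompatible roles, baseline covariate and outcome.

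Three consequences follow for the adjusted analysis.

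- **Target.** Conditioning on birth weight takes out whatever part of the effect acts through it. The 0.5 kg in the hypothesis is a total effect.
- **Confounding.** Randomisation does not balance the arms within levels of a post-randomisation variable. Common causes of birth weight and later growth can therefore bias the adjusted estimate. For the same reason it is not cleanly the effect that bypasses birth weight.
- **Trigger.** A variable enters because it differs between arms. A birth-weight difference may be chance or a PCS effect, so the rule brings birth weight in most often when prenatal supplementation has worked.

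**Working it through.** **Inputs from the protocol.** Total effect 0.50 kg; SD of infant weight 0.7 kg (quoted for 2 months); 85 evaluable infants, about 42.5 per arm (Section 7).

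**Assumptions, because the protocol gives no figures.** Birth-weight SD 0.45 kg; correlation r between birth weight and 3-month weight within arm 0.4 to 0.6; gain in birth weight from PCS, m, of 0 to 0.3 kg; two-sided alpha 0.05; comparison of means, although Section 8 speaks of medians; no common causes of birth weight and later weight.

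**The plan's own figure.** The standard error of a difference in means is 0.7 × √(2/42.5) = 0.152 kg. Power for 0.50 kg is Φ(0.50/0.152 − 1.96), about 0.91. Section 7 states 80%. That gap is a separate matter and nothing below depends on it.

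**Step 1: adjustment in every trial.** Slope b = r × 0.7/0.45, which is 0.622 at r = 0.4 and 0.933 at r = 0.6. Adjusted effect = 0.50 − b × m.

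- m = 0: 0.50 kg, nothing removed.
- m = 0.1: 0.50 − 0.062 = 0.44 and 0.50 − 0.093 = 0.41 kg (12% to 19% removed).
- m = 0.2: 0.50 − 0.124 = 0.38 and 0.50 − 0.187 = 0.31 kg (25% to 37%).
- m = 0.3: 0.50 − 0.187 = 0.31 and 0.50 − 0.280 = 0.22 kg (37% to 56%).

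**Step 2: how often the trigger fires.** The protocol sets no threshold for a difference between arms; p<0.05 is assumed. The standard error of the birth-weight difference is 0.45 × √(2/42.5) = 0.098 kg. The chance that birth weight enters is about Φ(m/0.098 − 1.96): about 18%, 54% and 87% for m = 0.1, 0.2 and 0.3. It is 5% when m = 0.

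**Step 3: adjustment only when triggered.** In simulation with the same inputs, the mean estimate of a true 0.50 kg effect, using the adjusted result when birth weight differs at p<0.05 and the unadjusted result otherwise, is:

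- m = 0.1: 0.46-0.47 kg.
- m = 0.2: 0.37-0.41 kg.
- m = 0.3: 0.24-0.33 kg.

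These are averages over trials. A single trial in which the trigger fires reports the adjusted estimate.

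**Step 4: power of the adjusted test.** Adjustment also reduces residual variance. The standard error becomes 0.7 × √(1 − r²) × √(2/42.5) / √(1 − q), where q = (m/2)² / ((m/2)² + 0.45²) is the squared correlation of arm with birth weight. Power with birth weight always in the model, against 0.91 without it:

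- m = 0: 0.95-0.98.
- m = 0.1: 0.88-0.91.
- m = 0.2: 0.71-0.75.
- m = 0.3: 0.40-0.57.

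**Sensitivity.** With birth-weight SD 0.5 kg and r from 0.3 to 0.7, the always-adjusted effect is 0.40-0.46, 0.30-0.42 and 0.21-0.37 kg for m = 0.1, 0.2 and 0.3.

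**The case against.** A reader might infer that the primary result itself is biased. The text does not support that. Section 8 names the intention-to-treat comparison first, and the multivariate analysis follows in its own sentence without being called the primary test. On that reading the unadjusted comparison stays intact and the fault lies in an accompanying estimate. The opposite reading is not excluded, because the rank of the two analyses is never stated. This part of the objection stands, and it limits the point to the adjusted analysis of the primary endpoint.

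A reader might also take a 12% to 56% loss as the expected damage. That range assumes adjustment in every trial and a real gain in birth weight. The written rule adjusts only when the arms differ, which lowers the average loss, most clearly at a 0.1 kg gain. The upper end needs a 0.3 kg gain, 60% of the whole hypothesised 3-month effect, from one to three months of supplement, and nothing in the protocol supports that value. With no effect on birth weight, adjustment costs nothing and raises power. This stands too: the lower bound is zero.

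An effect adjusted for birth weight may be of scientific interest. That would justify a separately labelled analysis, but it does not make birth weight a baseline variable. Nor is this a detail left open for a statistical analysis plan: the protocol names the covariate and misclassifies it, and no other section corrects it.

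**Conclusion.** The rule is wrong as written. Birth weight is measured after randomisation and after supplementation has begun, and Section 8 itself treats it as an outcome. Using it as a baseline covariate moves the adjusted analysis away from the total 0.5 kg effect of Section 7, and the imbalance trigger makes that most likely when the supplement has raised birth weight.

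The timing and the contradiction are certain from the text. The size is not. Under the assumptions listed, the loss runs from nothing, if PCS does not change birth weight, to 0.28 kg of 0.50 kg at the extreme of a 0.3 kg gain, a correlation of 0.6 and adjustment in every trial. Confounding by common causes is not included in these figures and could move the estimate either way. Whether the fault touches the principal conclusion depends on the rank of the adjusted model, which the protocol leaves open.

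**What to change.** In Section 8:

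1. Delete infant birth weight from the list of covariates.
2. Limit adjustment to variables measured before randomisation and named in advance, for example maternal CD4 and BMI at baseline, and drop selection by observed imbalance. Removing birth weight alone would leave that selection rule in place.
3. Keep weight at birth as an outcome compared between arms.
4. Label any birth-weight-adjusted model as an exploratory mediation analysis and state its assumption of no unmeasured common causes.
5. State whether the unadjusted or the adjusted comparison is primary.

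The cost is a few sentences of protocol text. Baseline CD4, height and weight are already collected, so no new data or visits are needed. If PCS in fact has no effect on birth weight, the price is the precision that adjustment would have brought: power of about 0.91 instead of 0.95-0.98 under the assumptions above.

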**3. Baseline studies.** All subjects will be given a standardized interview consisting of HIV medical history, and a standardized nutritional assessment (see Section 11) based on a 24-hour recall; a body composition evaluation (height, weight, 3-site skinfold thickness, circumference of upper arm, waist and hip); and laboratory studies (serum albumin, and CBC). Phlebotomy will be performed for CD4 count, and breast milk will be obtained for analysis. All subjects will receive nutritional counseling for pregnancy and breastfeeding and counseling on the risks and benefits associated with exclusive breastfeeding.

At the end of the baseline visit, each subject will be asked to complete a brief questionnaire known as the Informed Consent Evaluation and Feedback Tool (ICE-FT); this has been developed to improve comprehension of the informed consent process and measure how well subjects understand what the study involves and the risks/benefits of participation.

**4. Randomization and intervention.** A master randomization list will be generated by the Data Center at Dartmouth based on 1:1 assignment to PCS/MNS or MNS alone (control). Eligible subjects will be assigned a study number from the randomization list which will determine their assignment. Subjects in the PCS group will receive a supply of the PCS/MNS; subjects in the MNS group will receive a one month supply of MNS. In addition to the MNS women in both groups will be given a thermos for storing prepared foods.

**5. MNS and PCS.** Composition of the PCS is based on data obtained in Study 2-A. The caloric and protein intakes observed in Study 2-A were compared to recommendations of the World Health Organization (WHO) for pregnant and lactating women with HIV and the respective deficits in kcal/d and gm protein/d calculated. The PCS is formulated to cover the 75th percentile of the average calculated kcal and protein deficits in women from Study 2-A. All subjects will be counseled to continue their regular diets and consume the MNS and/or PCS as an additional supplement.

**MNS during pregnancy and lactation.** The MNS (micronutrient supplement) will be a tablet consisting of the standard Tanzanian Ministry of Health multivitamin (1 RDA) for pregnant and lactating women.

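### Baseline BMI is collected but not prespecified as a covariate for the secondary endpoint, and Section 8's only covariate rule for comparing arms depends on chance baseline imbalance

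*Protocol*

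**What the plan says.** Section 8 of the protocol (Data analysis) first deals with the primary endpoint: "For the primary endpoint, median infant weight, will be compared between the two groups at 3 months using intention to treat (ITT) methodology". The next sentence gives the covariate rule: "Multivariate analysis will be used to control for variables which differ between PCS and MNS treatment arms at baseline". Its examples are maternal CD4 and infant birth weight. The secondary endpoint comes directly after: "The secondary endpoint will be maternal BMI at the end of the intervention (6 months after infant birth"). It is a single value at one time point, and no test, model or covariate is attached to it.

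The covariate in question is available. Section 3 lists "a body composition evaluation (height, weight, 3-site skinfold thickness, circumference of upper arm, waist and hip") among the baseline studies for all subjects. Footnote b of Table 2 keeps height and weight in the shorter set of measurements taken during pregnancy. Section 8 also relies on BMI at entry elsewhere: "Subgroup analyses will be conducted on women entering the study in the lowest BMI quartile".

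Footnote a of Table 2 bears on the quality of that baseline value: "Number of monthly pre-natal visits will vary from 1-3 depending on how early mother is enrolled in third trimester". It adds that the baseline visit will, when possible, coincide with the visit three months before delivery.

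**The concern.** A woman's BMI on entry is likely to be among the best predictors of her BMI at 6 months after birth. A rule that selects covariates by whether the arms happen to differ ignores this. After randomisation, baseline differences arise by chance, so the rule picks covariates for their imbalance and not for their prognostic value. If it governs the BMI comparison, and a difference means p<0.05, baseline BMI enters the model in about 1 trial in 20. If it does not govern the BMI comparison, the protocol prespecifies no adjustment for it at all. Under neither reading is the useful covariate fixed in advance.

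At stake is the precision of the trial's only secondary endpoint, in a study of 96 women. An adjustment chosen after looking at baseline tables also leaves the analyst a choice that one sentence would remove.

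**Working it through.** **The plan's own figure.** There is none for this endpoint. The only power statement, in Section 7, concerns infant weight at 3 months and has no bearing here.

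**Inputs from the protocol.** 96 women randomised 1:1, 48 per arm (Section 7). Primary endpoint expected on 85 infants (Section 7).

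**Assumptions, none given in the protocol.**
- 43 women per arm with BMI at 6 months, carried over from 85/2 = 42.5 infants per arm at 3 months.
- SD of 6-month BMI 4 kg/m2, with 3 to 5 as a range.
- Two-sided alpha 0.05.
- Correlation r between baseline and 6-month BMI of 0.5, 0.6 or 0.8.

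**Step 1: detectable difference.** Adjusting for baseline multiplies the residual variance by (1 − r²). The difference detectable with 80% power is then

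MDD = (1.960 + 0.842) × SD × √(1 − r²) × √(2/43), with √(2/43) = 0.2157.

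Unadjusted, SD 4: 2.802 × 4 × 0.2157 = 2.42 kg/m2.

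| r | variance removed (r²) | √(1 − r²) | MDD, SD 3 | MDD, SD 4 | MDD, SD 5 | equivalent sample size, 1/(1 − r²) |
|---|---|---|---|---|---|---|
| unadjusted | 0% | 1.000 | 1.81 | 2.42 | 3.02 | 1.00 |
| 0.5 | 25% | 0.866 | 1.57 | 2.09 | 2.62 | 1.33 |
| 0.6 | 36% | 0.800 | 1.45 | 1.93 | 2.42 | 1.56 |
| 0.8 | 64% | 0.600 | 1.09 | 1.45 | 1.81 | 2.78 |

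For an illustrative true difference of 1.5 kg/m2 at SD 4, power is 41% unadjusted and 52%, 59% and 83% at r = 0.5, 0.6 and 0.8.

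**Step 2: what the imbalance rule recovers.** A simulation of 20,000 trials per setting, 42 women per arm, compared three analyses: never adjusting, adjusting only when the baseline difference has p<0.05, and always adjusting. The true effect was 0.4 SD for power and zero for type I error. The rule triggered in about 5% of trials.

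| r | power, never | power, imbalance rule | power, always | type I error, imbalance rule |
|---|---|---|---|---|
| 0.6 | 44% | 45% | 62% | 3.8% |
| 0.8 | 45% | 46% | 86% | 3.0% |
| 0.9 | 44% | 47% | 99% | 2.1% |

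So the rule, read this way, recovers almost none of the gain. It also makes the test conservative.

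**Step 3: how strong must r be?** Half of the variance is removed only when r² = 0.5, that is r = 0.71. The standard error is halved only when √(1 − r²) = 0.5, that is r of about 0.87.

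**The case against.** The strongest reply is that the protocol never says the imbalance rule applies to BMI. The rule stands between the primary-endpoint sentence and the BMI sentence, and infant birth weight, one of its examples, points to infant weight as the outcome. If the rule belongs only to the primary endpoint, what remains is an unspecified model for a secondary endpoint, which a protocol may leave to an SAP. This stands in part: applying the rule to BMI is an inference. But the rule is the only one that Section 8 offers for comparing the arms, and an SAP author following the protocol could well carry it over. The document should close that off.

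A reader might infer three stronger things that the documents do not support.

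- *That most of the available precision is thrown away.* This needs r above about 0.71. The protocol gives no r, and a third-trimester BMI at varying gestation may track later BMI less closely than a non-pregnant value. At r = 0.5 the gain is moderate.
- *That the false-positive rate is inflated.* Given one particular baseline imbalance of 1.5 standard errors, the unadjusted test rejects in about 8% to 10% of null trials for r between 0.7 and 0.9. That is conditional on the imbalance. Over all randomisations the unadjusted test holds 5% and its estimate is unbiased.
- *That a 6-month value is the wrong endpoint.* ANCOVA uses the same endpoint, and nothing in Section 8 rules it out.

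The variation in gestation is also smaller than footnote a's first clause suggests, since the baseline visit is meant to fall at the earliest third-trimester visit when possible. A gestational-age term is a sensible refinement, not the core of the point.

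**Conclusion.** The point holds as a matter of efficiency. The protocol measures baseline height and weight in every woman, does not prespecify baseline BMI as a covariate for its only secondary endpoint, and states one covariate rule for comparing arms, which is a poor one. Prespecified adjustment reduces the variance by about r²: 25% to 64% for r from 0.5 to 0.8. At SD 4 kg/m2 and 43 women per arm, that moves the detectable difference from 2.4 to between 2.1 and 1.45 kg/m2. The SD, r and the number of mothers at 6 months are assumptions. The direction does not depend on them, apart from the trivial cost of one degree of freedom, but the size does. Without adjustment the comparison remains valid; it is less precise than the collected data allow.

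**What to change.** Add to Section 8: maternal BMI at 6 months will be compared between arms by ANCOVA with terms for arm and baseline BMI, and gestational age at the baseline measurement where available, whether or not the arms differ at baseline. State that the imbalance-triggered rule does not apply to this endpoint.

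The cost is one or two sentences. Height and weight are already scheduled at baseline and at month 6, so no extra visits or participants are needed. Gestational age is proposed only where it is recorded: Table 2 lists an ultrasound at baseline, but the protocol does not say that it is used for dating. The wording should be settled before any outcome data are seen by arm. If an SAP exists, it should carry the same model.
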